#### Website Engagement and Feedback: Implicit and Explicit

We will use repeated use over other use measures (number of logins) to measure website engagement, as this has demonstrated an association with smoking cessation [39]. This is an ordinal scale of the number of Decide2Quit functions used after the first DISC visit (0: no functions used; 1: use of 1-2 functions, 2: >2 functions used). We will also continuously assess explicit (influence survey) and implicit (days to click on website) feedback after each email sent. When a smoker is sent an email, we will include a link to rate the message on the influence scale.

### Sample Size

#### Hypothesis 1: Dissemination

Our previous work [26,27] showed that having access to peer recruitment increased the proportion of African Americans to 23%, compared to 11% in the initial seeds (those recruited by advertisements). Using 10% as the base rate in the nonpeer recruitment group (no access to peer recruitment), we estimated sample size requirements by varying the proportion in the peer recruitment from 16% to 20%. With these assumptions, for our primary aim, we will need 219 smokers in each group to detect a difference of 10% (power=80%, α=.05). If we reduce the difference to 8% and 6%, we will need 319 and 525 participants in each group, respectively. Given that we will work with our panel to encourage recruitment of African American smokers in the peer recruitment group and may see bigger differences than those in our pilot study, we will have adequate power, particularly with the proposed sample size of 600 in each recruitment method. For recruitment time, previous trials estimated that the mean number of days to recruit a sample of 700 smokers was 244 (SD 81) days [27,40]. Assuming that peer recruitment proceeds with the same rate and SD, we can detect a difference in recruitment time as low as 14 days. Since we expect the comparison rate to be much slower, we are adequately powered to detect differences with a sample of 600 (power=80%).

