## Methods

### Study Overview

The goal of this study (ClinicalTrials.gov: NCT03224520) is to recruit 1200 smokers to test our effectiveness and dissemination hypotheses. To participate in the study, all smokers will register online for the Decide2Quit DISC. Randomization will occur after registration using a multilevel approach, as detailed below. We will follow smokers for 6 months from their registration date. Following a description of the intervention and comparison, our protocol is described in detail below. The protocol of our study was approved by the Institutional Review Board at the University of Massachusetts Medical School.

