**Figure 1 figure1:**
[figure not shown]
Flow of participant randomization. Allocation to receive the peer recruitment tools occurs in two phases or waves. Wave 1: Half of the enrolled smokers are randomized to receive peer recruitment tools, while the others do not receive the tools; and Wave 2: All subsequent smokers who are randomized to the effectiveness trial and also report they were peer-recruited are given access to the peer-recruitment tools.

The basic flow of a single hypothetical smoker through the peer-referral, registration, and subsequent initiation of new peer-recruitment is described in Figure 1. Peer recruitment will take place in waves. As is common in peer recruitment approaches, to initiate the waves, we will recruit the first wave (wave 0 or seeds) of smokers. Seeds will be recruited using online advertisements. Once a seed registers on Decide2Quit and receives the peer recruitment toolset, we expect the following to occur:

The seed consents to be in the study and recruit smokers from his/her network using the peer-recruitment tools (by sending a Facebook private message).The successfully peer-recruited smoker (wave 1 recruit) registers on the system and consents to recruit other smokers in his/her social network.The wave 1 recruit then continues the peer-recruitment chain, recruiting smokers his/her their social network.The successfully peer-recruited smoker then registers (wave 2 recruit). The waves progress until the target sample size is reached.

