### Study Design

As noted in Figure 1, all participants registering online on the Decide2Quit DISC will first undergo an effectiveness randomization and then a peer recruitment allocation. The effectiveness randomization will randomly assign participants to either receive access to the recommender system CTHC or the standard CTHC. The peer recruitment allocation will depend on the recruitment source. As noted in the section below, we will either directly recruit participants to the study (via search engine advertisements and research match) or they will be recruited by their peers (peer recruited). Directly recruited peers will be randomized to either receive the peer recruitment toolset or not receive the toolset. All peer recruited participants will receive access to the peer recruitment toolset. We are using this approach for the peer recruited smokers to enhance blinding. This decision was made because these recruited smokers may communicate with their peers about the intervention.

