#### Hypothesis 2: Repeated Use of Website

We used the method published by Whitehead to calculate power for this hypothesis [41]. In our previous work, we found a linear association between the 6-month cessation and repeated use by using the repeated use scale. For every increase by one in this scale, odds of smoking cessation increased (OR 2.10, 95% CI 1.03-4.30) [39]. With the current sample size of 300 per group, we can detect a difference a cumulative odds ratio of 1.7. Thus, our study is adequately powered to measure a reasonable difference in the repeated use measure.

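### The H1A and H2 sizing ignores that every peer recruit enters the toolset arm, so no level of peer recruitment gives both stated group sizes and a non-zero H1A effect

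*Protocol article*

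**What the plan says.** All places are in the protocol article.

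- **Total.** The Study Overview sets the goal to "recruit 1200 smokers to test our effectiveness and dissemination hypotheses". The text under Figure 1 says "The waves progress until the target sample size is reached", so peer recruits count toward the 1200.
- **Allocation.** Study Design: "Directly recruited peers will be randomized to either receive the peer recruitment toolset or not receive the toolset". The Figure 1 caption gives the ratio: "Half of the enrolled smokers are randomized to receive peer recruitment tools, while the others do not receive the tools". For recruits, Study Design says "All peer recruited participants will receive access to the peer recruitment toolset".
- **H1 sizing.** Sample Size, Hypothesis 1 describes the control as follows: "Using 10% as the base rate in the nonpeer recruitment group (no access to peer recruitment". It takes 16% to 20% for the peer recruitment side and needs 219, 319 or 525 per group for differences of 10, 8 or 6 points. It then calls power adequate, "particularly with the proposed sample size of 600 in each recruitment method".
- **H2 sizing.** Sample Size, Hypothesis 2: "With the current sample size of 300 per group, we can detect a difference a cumulative odds ratio of 1.7".
- **Analysis.** Statistical Analyses compares the peer recruitment groups with the standard groups by chi-square for H1A. Peer recruited against directly recruited smokers is a secondary analysis within the peer recruitment groups.

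**The concern.** Equal groups by toolset access and four equal cells would follow if all 1200 participants were randomised to the toolset. They are not. Only directly recruited smokers are, and each peer recruit adds to the toolset side alone while using up one of the 1200 places. Peer recruitment, which produces the H1A effect, is thus what destroys the group sizes used to power it.

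The assumed effect has a related weakness. The Hypothesis 1 sizing text attributes the pilot's 23% to having access to peer recruitment. The section on the peer recruitment toolset gives 23.8% as the share among smokers recruited by peers, against 10.8% among those recruited directly. In this trial the toolset arm also holds half of the directly recruited smokers, which dilutes its share.

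At stake is how a null result would be read. A reader who trusts 600/600 and 300 per cell could take a null H1A or H2 finding as evidence against an effect that the realised sizes could not detect.

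**Working it through.** **1. The plan's own figures.** For 10% against 20%, 18% and 16%, two-sided α = 0.05 and 80% power, the two-proportion formula with continuity correction gives 219, 319 and 525 per group, an exact match. At 600/600, power without continuity correction is 99.8%, 98.0% and 87.2%. The H2 odds ratio of 1.7 cannot be uniquely reproduced because the category distribution is not given. Whitehead's formula at 300/300 gives 1.52 (equal thirds) to 1.77 (80/10/10), so 1.7 is attainable and is taken as given below.

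**2. Group sizes.** Let R be the peer recruits and D = 1200 − R the directly recruited.

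- No toolset: D/2 = (1200 − R)/2
- Toolset: D/2 + R = (1200 + R)/2
- Difference: R

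So 600/600, and 300 in each of the four cells after the 1:1 CTHC randomisation, requires R = 0. Both arms are then random halves of the same directly recruited pool, and the expected H1A difference is zero.

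**3. The other reading of the 600s.** If they are 600 recruits and 600 directly recruited smokers, then R = 600, the access groups are 900 and 300, and the H2 cells are 450/450/150/150, not 300 each.

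**4. H1A with dilution.** A seed here is a directly recruited smoker with the toolset, and r is recruits per seed over the whole chain. Then R = rD/2, D = 1200/(1 + r/2), and the toolset-arm share is (10% + r × 23.8%)/(1 + r). The pilot ratio is 569/190 = 2.99, close to r = 3. Power is for the pooled two-proportion test with 10% in the control group.

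| r | R | toolset / no toolset | toolset-arm share | power |
|---|---|---|---|---|
| 0.25 | 133 | 667 / 533 | 12.8% | 32% |
| 0.5 | 240 | 720 / 480 | 14.6% | 65% |
| 1 | 400 | 800 / 400 | 16.9% | 91% |
| 2 | 600 | 900 / 300 | 19.2% | 98% |
| 3 | 720 | 960 / 240 | 20.4% | 98% |

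If the plan's 16%, 18% or 20% is the share among recruits, maximum power over all R is 44%, 67% and 84%. For 20%, 80% is reached only for R of about 540 to 866. For 23.8%, it is reached for R of about 310 to 1052.

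If 16%, 18% or 20% is the rate in the whole toolset arm, imbalance alone gives 82%, 97% and 99.6% at 800/400, and 67%, 88% and 97.5% at 960/240.

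**5. H2.** Scaling from the plan's own figure: detectable ln OR = ln(1.7) × √(150 / [n₁n₂/(n₁+n₂)]), where 150 = 300 × 300/600.

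| contrast | R = 600 | R = 720 |
|---|---|---|
| toolset cell vs standard cell | 450 vs 150: 1.85 | 480 vs 120: 1.94 |
| H2C as recommender-only vs standard cell | 150 vs 150: 2.12 | 120 vs 120: 2.31 |
| H2C as all recommender participants vs standard cell | 600 vs 150: 1.81 | 600 vs 120: 1.92 |

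Worked case, 480 vs 120: n₁n₂/(n₁+n₂) = 96, √(150/96) = 1.25, exp(0.5306 × 1.25) = 1.94.

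**6. H1B.** With SD 81 days, the detectable difference is 2.80 × 81 × √(1/n₁ + 1/n₂): 13.1 days at 600/600, 13.9 at 800/400 and 16.4 at 960/240, against the stated 14.

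**The case against.** The strongest reply is that H1A is well powered where the trial was expected to land. At the pilot's referral ratio and the pilot's share among recruits, power is about 98% despite the 960/240 split. A 10-point difference in the whole arm still has 97.5%. This stands. A reader might infer from the impossible group sizes that H1A is simply underpowered. The documents do not support that, because power turns on R and the recruit share, and the protocol fixes neither.

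Second, the wording about each recruitment method can mean recruits against directly recruited smokers. This fits H1A's contrast with standard online recruitment, and 600/600 then occurs at R = 600 with 87% to 99.8% power. So it would be too strong to say that 600/600 arises only with no peer recruitment on every reading. But this reading conflicts with the no-access control in the same paragraph, makes the powered contrast one that Statistical Analyses calls secondary, and still contradicts 300 per H2 cell.

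Third, H2C does not say which recommender participants it compares. The 2.31 depends on taking the recommender-only cell. Read as a main effect of CTHC (600 vs 600), the detectable odds ratio would be about 1.46, better than 1.7. The pooled reading against the standard cell is worse than 1.7 only above R = 400, where 600 vs 200 gives exactly 150 in the scaling formula. This stands, and H2C should be reported under each reading.

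Finally, clustering by recruiter would lower H1A power further, but the protocol gives no intraclass correlation, so no single figure can be attached.

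**Conclusion.** The concern holds as an inconsistency in the sizing. No value of R yields 600/600, four cells of 300 and a non-zero H1A effect together. The stated sizes therefore do not establish the power claimed for H1A, nor the odds ratio of 1.7 for the H2 comparisons of a toolset cell with the standard cell.

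For H1A the consequence is conditional: low power if recruitment is below about one recruit per seed at a 23.8% share, or if recruits are only 16% to 18% African American, and ample power at pilot performance. For H2, comparing a toolset cell with the standard cell weakens for every R above zero, modestly up to R = 400 (1.76) and more beyond. H1B is little affected.

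Assumptions: an exact 1:1 split, 10% African American among directly recruited smokers in both halves, no design effect, 1200 in total, and an H2 category distribution consistent with the plan's 1.7.

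**What to change.** 1. Define the H1A groups once, by access arm, and use that definition in the hypotheses, the sizing and the analysis.
2. Remove 600 in each recruitment method and 300 per group as the basis for the toolset contrasts.
3. Replace them with a table over recruits per seed (0.25, 0.5, 1, 2, 3) giving R, the access group sizes, the four cell sizes, the diluted toolset-arm share, H1A power and the H2 detectable odds ratio.
4. State which cells H2C compares.
5. Give any allowance for clustering by recruiter as a range of assumed intraclass correlations, labelled as assumptions.
6. In the results, report achieved cell sizes and confidence intervals for the contrasts, not post hoc power.

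The cost is text and recalculation, and some stated figures become less favourable. No participants are added and the design does not change.

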#### Hypothesis 2: Repeated Use of Website

We used the method published by Whitehead to calculate power for this hypothesis [41]. In our previous work, we found a linear association between the 6-month cessation and repeated use by using the repeated use scale. For every increase by one in this scale, odds of smoking cessation increased (OR 2.10, 95% CI 1.03-4.30) [39]. With the current sample size of 300 per group, we can detect a difference a cumulative odds ratio of 1.7. Thus, our study is adequately powered to measure a reasonable difference in the repeated use measure.

#### Hypothesis 3: Effectiveness

We assumed a control cessation rate of 15% [42], and a two-sided significance level of .05. A sample size of 300 in each group will achieve 80% power to detect a difference of 9% (quit rate in intervention=24%) in quit rates between the two groups, based on a Z-test with pooled variance. We will categorize the NicAlert test results into smokers and nonsmokers and use the chi-square statistic to test for differences. We calculated the detectable difference in risk reduction with 300 smokers in each group and a mean of 3.3 cigarettes in the comparison group, using SDs of 2 and 3 with 80% and 90% power, respectively. We will have 90% power to detect a difference of 0.80 (or smaller) in the number of cigarettes smoked between the two groups. This difference is likely to be achieved based on the results of our PCORI pilot, in which we achieved a reduction of 0.85 (4.15-3.3) in 30 days compared to smokers receiving the standard CTHC messages; smokers receiving the recommender CTHC had a higher reduction in the number of cigarettes at 30 days (Standard CTHC: mean 3.3; S2S adaptive CTHC: 4.15).

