**Baseline measures**			
	Demographics	Age, gender, race, ethnicity, education level Contact Information	Reach
	Smoking habits	Current smoking habits	Reach
	Quit attempts	Readiness to quit Nicotine dependence Nicotine replacement therapy use E-cigarette use	Reach
	Family-based intervention and social network	Household status Smokers in social network Interest in family-based intervention	Reach
	Reach and registration	Number of users who saw and clicked on online advertisements Number of users who registered following online advertisements	Reach, Adoption

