#### Effectiveness Outcomes

##### Smoking Cessation: 7-Day Point Prevalence and Verification by Saliva Test NicAlert

The primary outcome measure will be 7-day point prevalence at the 6-month follow-up. The 7-day point prevalence will be assessed by asking, “Do you currently smoke cigarettes (smoked even 1 puff in the last 7 days)?” [33] The 7-day window provides an appropriate stringent measure to account for a cross-sectional snapshot. In a cessation trial, biochemical verification is used to monitor for differential misclassification by the randomization group. The degree of misclassification is moderated by characteristics of the smoking cessation intervention [34]. Studies that are in-person and intense generally have more misclassification because of the personal connection between the smoker and the counselor and therefore require biochemical verification. Less misclassification occurs in low intensity, light-touch studies. Further, differential misclassification increases with intervention differences between two groups. Since our intervention and control are both texting interventions, the potential for differential misclassification is reduced. Further, requiring biochemical verification can, in fact, lead to additional issues, including refusal to participate, thus biasing the sample [34,35]. However, based on peer review, we are conducting biochemical verification. To reduce the potential for biasing the sample due to the need for biochemical verification, we are using an opt-in procedure to conduct biochemical verification among those who indicated they had quit smoking at 6 months. If a participant indicates they have quit smoking at 6 months, they are contacted by the research study staff to see if they would like to opt-in to the biochemical verification. If a participant opts in, they will be mailed the NicAlert test strips (Nymox Corporation, St Laurent, Quebec, Canada) within 24 hours with clear instructions on how to take a picture and return the picture of the results to us electronically. NicAlert is a semiquantitative method that uses a dipstick to measure the level of cotinine in a sample of saliva. The test strip displays the result in seven zones. Each zone represents a range of levels of cotinine/smoking (eg, zone 0: 0-10 ng/mL, a nonsmoker, zone 6: >1000 ng/mL, a heavy smoker). The results will be read as 0-6, and as recommended, any value ≥ 1 will be considered as tobacco use [36-38]. Our staff will also be available by phone to help the smokers complete testing. Participants sending back the sample will receive an additional US $50 incentive (as outlined in the consent form) for completing biochemical verification.

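### The NicAlert chi-square compares confirmation rates among volunteering self-reported quitters, not verified quitting by arm, and its cut-off makes no exception for abstainers who use nicotine products

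*Protocol article*

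**What the plan says.** The primary outcome is self-reported 7-day point prevalence at 6 months, and the question asks about cigarettes. It is analysed by generalized linear models, and primary analyses are intent-to-treat.

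The section on smoking cessation and verification gives the purpose of biochemical testing as monitoring for misclassification that differs between randomised groups. To limit refusal bias, the investigators are "using an opt-in procedure to conduct biochemical verification among those who indicated they had quit smoking at 6 months". NicAlert zone 0 (0–10 ng/mL) is a nonsmoker, and "any value ≥ 1 will be considered as tobacco use".

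The analysis appears twice, both times under Hypothesis 3: in the sample size section ("We will categorize the NicAlert test results into smokers and nonsmokers and use the chi-square statistic to test for differences") and, in nearly the same words, in the Statistical Analyses section. Neither place gives a denominator.

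Table 1 lists "Nicotine replacement therapy use E-cigarette use" among the baseline measures. Its 6-month rows are the cessation question and the NicAlert test.

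**The concern.** A test result can exist only for someone who reported quitting and then agreed to be tested. Both events follow randomisation, and the intervention may affect both. A chi-square on those results therefore no longer compares the randomised groups. It asks whether volunteers' quit claims are confirmed equally often in the two arms. Placed under the effectiveness hypothesis, it invites the reader to treat it as the biochemical counterpart of the quit-rate comparison.

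Two errors of interpretation could follow. A non-significant result could be read as failure to confirm a real effect, or as reassurance that misreporting is balanced when the test had little chance of showing otherwise.

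The cut-off adds a second problem. Cotinine is a breakdown product of nicotine whatever its source, so a person who has stopped cigarettes but uses nicotine replacement or an e-cigarette can read 1 or more. The primary question would rightly count that person as abstinent; NicAlert would label the same person a smoker. If such use differs by arm, the check would signal differential misreporting where there is none.

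**Working it through.** **Inputs from the article.** Control quit rate 15%, intervention 24%, 300 per group, 80% power, "a two-sided significance level of .05", "based on a Z-test with pooled variance". The total is 1200 and Hypothesis 3 contrasts A+B with C+D, so about 600 per arm if allocation is 1:1.

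**Assumed, because the article gives no figure.** Opt-in rate, disconfirmation rate, and nicotine product use among abstainers.

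**Formula.** Power = Φ{(|p1 − p2| − 1.96·SE0)/SE1}, where p̄ is the pooled proportion, SE0 = √[p̄(1 − p̄)(1/n1 + 1/n2)] and SE1 = √[p1(1 − p1)/n1 + p2(1 − p2)/n2].

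**1. The plan's own figure.** With 15% v 24% and 300 per group, p̄ = 0.195, SE0 = 0.0323 and SE1 = 0.0321. Power = Φ{(0.09 − 0.0634)/0.0321} = 79.6%, so the stated 80% is right. At 600 per arm it is 97.7%. Both figures apply to self-reported quitting over everyone randomised, not to the NicAlert chi-square.

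**2. What the chi-square measures.** With 600 per arm, 15% and 24% give 90 and 144 self-reported quitters. Suppose all are tested and 90% are confirmed in each arm: 81/90 and 129.6/144. The chi-square compares 90% with 90% and expects no difference. Over all randomised participants the verified rates would be 13.5% and 21.6%. The two quantities are different.

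**3. Power as a misclassification check, 10% v 20% disconfirmed.** At 40–50% opt-in and 600 per arm, 36–45 are tested in the standard arm (90 × 0.40 to 90 × 0.50) and about 58–72 in the recommender arm (144 × 0.40 to 144 × 0.50). Rounding the whole range to 35–70 per arm:

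| Tested (arm 1 / arm 2) | Power |
|---|---|
| 35 / 35 | 21% |
| 70 / 70 | 38% |
| 45 / 72 (50% opt-in at 600 per arm, or full opt-in at 300) | 28% |
| 90 / 144 (full opt-in at 600 per arm) | 53% |

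For 35 per arm: p̄ = 0.15, SE0 = 0.0854, SE1 = 0.0845, and Φ{(0.10 − 0.1673)/0.0845} = 21%. In the unequal rows the larger arm has the 20% rate. With the rates swapped, the last row gives 57%. For 80% power against 10%, the other arm's disconfirmation rate would have to be about 38% (35 per arm) or 28.5% (70 per arm).

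**4. Verified abstinence over all randomised, untested quitters counted as not verified, 600 per arm.**

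| Opt-in | Disconfirmed | Verified rates | Power |
|---|---|---|---|
| 100% | 0% | 15% v 24% | 97.7% |
| 50% | 0% | 7.5% v 12% | 75% |
| 50% | 10% | 6.75% v 10.8% | 70% |
| 25% | 0% | 3.75% v 6% | 44% |

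**5. Nicotine products.** Take full opt-in, no false reports, and readings of 1 or more in every product user. If 10% of standard-arm and 30% of recommender-arm abstainers are users, verified rates are 15% × 0.90 = 13.5% and 24% × 0.70 = 16.8%: the 9-point difference becomes 3.3 points. With the shares reversed it is 10.5% v 21.6%, or 11.1 points. In the first case the chi-square sees 10% v 30% disconfirmed although nobody misreported, and with 45 and 72 tested it would call that significant with 74% probability.

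**The case against.** The strongest reply is that the contrast suits its stated purpose. If verification is meant to detect differential misclassification, comparing readings by arm among self-reported quitters is the natural comparison, and finding no difference in step 2 is the right answer to that question. This stands. What remains is that the test sits under the effectiveness hypothesis and is weak even for its own purpose.

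Opt-in is also a disclosed and reasoned choice, supported by an incentive and telephone help. That stands, and no change to it is needed.

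The denominator is not stated, so counting untested participants as smokers is not strictly excluded, and an article may leave such detail to a fuller document. But both sections speak of categorising test results, which the untested do not have. The point rests on that wording, not on the missing detail.

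Table 1 is not a complete list: it omits the 6-month cigarette count that the risk-reduction outcome needs. So it does not prove that nicotine products go unasked at 6 months. It shows only that none is listed there. The cut-off as written has no exception either way.

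A reader might infer more than the article supports:
- That any cotinine counts as smoking. It does not; zone 0 reaches 10 ng/mL.
- That the primary result is compromised. It is self-reported, and nothing lets NicAlert override it.
- That the messages steer one arm towards nicotine replacement. The article gives only a coding category for over-the-counter and prescription treatments, and both arms draw on one message database. Selection differs between the systems, so an imbalance is possible but not shown.

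**Conclusion.** The point holds for a supporting analysis and is moderate in weight. As written, the NicAlert chi-square compares confirmation rates in a self-selected, post-randomisation subset. It can inform on differential misclassification but cannot serve as a randomised comparison of verified quitting. Its power for 10% v 20% disconfirmation is about 21–38% with 35–70 tested per arm, and 53–57% at best with 600 per arm. These figures rest on assumed opt-in and disconfirmation rates and on the article's own 15% and 24%.

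The cut-off counts cigarette-abstinent users of nicotine replacement or e-cigarettes as smokers. The size and direction of any resulting difference between arms are unknown; step 5 is an illustration, not an estimate. The self-reported primary analysis and its stated power are unaffected.

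**What to change.** 1. Describe the NicAlert comparison as a check on misclassification. Report opt-in, return and disconfirmation rates by arm with confidence intervals, and state that a non-significant chi-square will not be read as reassurance.
2. Add a supporting analysis of verified abstinence, defined as self-reported quit plus zone 0, over all randomised participants with the primary model and an explicit rule for the untested. Add a sensitivity analysis that applies each arm's observed disconfirmation rate to its untested quitters.
3. Ask about current nicotine replacement and e-cigarette use when the test is done. Report readings of 1 or more in users as a separate category instead of as smoking.

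The cost is wording plus one or two survey questions. The verified endpoint depends on who opts in, so differential opt-in could create or hide a difference. It also has less power than self-report: about 75% at an assumed 50% opt-in with 600 per arm, and less if some tests disconfirm, against 97.7%. It should therefore be supporting only. If data collection has closed, parts 1 and 2 can still be done, and part 3 becomes a stated limitation unless the 6-month questionnaire already asked.
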